**Quality of care assessments**

Health facility assessment will be conducted bi-annually to provide information on facility level performance and service quality including availability of commodities and supplies, human resource and key equipment as well as observation of HCPs will be done using quality of care checklists to assess the effectiveness of training provided. In case of inadequate availability of resources or sub-optimal quality of care provided, arrangements for supplies will be done by liaising with stakeholders and refresher training will be provided to HCPs. All public health facilities (509, including 19 maternal and CH centres, 150 government dispensaries, 255 BHUs, 59 RHCs, 18 THQs, 6 DHQs and 2 civil hospitals) will be included in the study. For private providers, all health practitioners who provide services according to district theme will mapped. Practitioners with high patient flow will be included in the study for quality assessment and need-based support will be ensured.

**Assessment of the community outreach programme (ie, LHW programme**)

The activities of LHWs will be monitored on a regular basis to strengthen monitoring system of LHW programme and improve LHW functionality. Thirty per cent health facilities will be selected on a quarterly basis, and 10 LHWs will be selected using purposive sampling from each health facility. Data will be recorded in a mobile application from the LHW’s source registers for community support groups and 10 randomly selected households (*khandans*). The data for community support groups will be validated from the community and households will be visited to validate the household level data.

### Study outcome measures

The primary outcomes of interest are reduction in PNM rate (20% compared with baseline) and at least 30% reduction in diarrhoea and pneumonia case fatality rates. The secondary outcomes include coverage of essential intervention across the continuum of care and maternal, newborn and child morbidity rates (table 2).

### Analysis plan

#### Data management

A custom-made mobile application will be designed to collect data using Android handheld devices. The data collected in the field will be stored and accessible real time at AKU server. Android-based application will be designed such that it can monitor the location of the data points, time at which data was collected and time taken to fill each form. This will enable the data management unit consisting of IT specialists and statisticians to monitor data collection activities and quality. Furthermore, data cleaning will be done by identifying errors and missing entries before any analysis begins.

#### Statistical analysis

Basic frequencies will be calculated for demographic, social equity, primary outcome and secondary outcome of the study at baseline, and midline surveys and endline surveys. Furthermore, the baseline data will be analysed using multivariate analytical methods to assess the perinatal and child mortality estimates and its determinants.

The overall impact of the UeN project will be measured assuming parallel trends within the two MNH and CH groups, in the absence of any intervention, difference-in-difference estimates will be used to assess the impact of the intervention on outcomes. An interaction term between group (intervention/control) and survey wave (baseline/end-line) will be included in each model. All the analyses will be done using Stata.

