**Trial registration number:**

NCT04184544; Pre-results.

Strengths and limitations of this studyStrength of the Umeed-e-Nau project includes its quasi-experimental study design with district representative sample size.The household surveys will be powered to measure district level perinatal and child mortality estimates.Interventions to promote use of data for decision-making will be assessed in Pakistan for the first time.Potential limitations include challenges in accessing routine service delivery data for evaluation purposes.Challenges of working with or assessing role of lady health workers who are already overburdened with competing priorities.

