An LHW is associated with the public health facility usually at the primary level and secondary level. Each LHW has a catchment population comprising of approximately 200 households.^11^ They target specific groups such as families with children under five and married couple eligible for family planning. Their key functions include increasing awareness about contraception, MNCH and nutrition. They also provide treatment for common illnesses like diarrhoea and acute respiratory infections (ARI), and distribute contraceptives for family planning. Furthermore, they identify danger signs for illnesses and refer people from the community to the health facility.

Around 70% of the population uses private providers, with expenses often paid out of pocket. Private providers are largely unregulated, though provincial governments have recently set up regulatory healthcare commissions to reduce high levels of unqualified providers and initiated licensing of private facilities.^1^

A number of strategies have been employed at community and facility levels to strengthen the public health service delivery system in Pakistan and elsewhere to improve the MNCH indicators.^12^ Such approaches have attempted to improve the quality of care through reviewing and updating training material^13^; conducting training and providing essential commodities to healthcare providers (HCPs) and community health workers (CHWs).^14^,^15^ For example, job aids-led intervention to improve quality of antenatal counselling in the Zou/Collines regions of Benin showed positive impact on danger sign recognition, birth preparedness, clean delivery and newborn care.^16^ Training of HCPs improved contact and quality across the continuum of care in Ghana.^17^ Furthermore, capacity building initiatives for healthcare workers have resulted in improved care quality of MNCH services in Jigawa State, northern Nigeria.^18^ Provision of job aids and training of LHWs in Gilgit region of Pakistan resulted in a significant reduction of 38% in perinatal mortality (PNM) rate.^19^ Furthermore, birth kits with 4% chlorhexidine for application to the umbilical cord were provided to traditional birth attendants to prevent omphalitis, thereby resulting in 38% reduction in neonatal mortality.^20^ A diarrhoea pack with oral rehydration salts (ORS) and amoxicillin was distributed. This was feasible and acceptable with an impact on the incidence of diarrhoea and reduced hospitalisation rates.^21^

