### Study design

In order to evaluate the impact of scaling up MNCH interventions, a quasi-experimental study design will be used. Each of the eight districts will be treated as an intervention site, and will be grouped together broadly into two areas to span MNCH interventions (figure 3). As detailed below, group 1 will receive maternal and newborn health (MNH) interventions, while group 2 will receive CH interventions. Each group will serve as the ‘control’ for the other. This design will help us evaluate independent and combined effect of MNCH interventions to address MNCH outcomes.

Site allocation to group 1 and 2 were done through extensive consultation with provincial government, bilateral donors and UN agencies, and UeN project team. Factors that were considered during intervention allocation included level of MNCH morbidity and mortality, assuring geographical diversity across the provinces, varying size of the districts and government MNCH priorities in those districts (so that those areas that were focused on improving CH, for example, received the CH interventions). This design might have ethical implications such as not providing all MNCH related evidence-based interventions to the entire population; however, population in control areas will continue to receive all the routine services which are part of the public sector standard of care and some additional MNCH intervention as per allocation to the type of intervention group. Furthermore, this ethical concern has been addressed by developing partnerships with Government, development agencies and private providers who have agreed to include UeN interventions in the existing health system, if the evidence generated suggests their effectiveness and feasibility when delivered at scale.

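### With each treated group as the other's control, the difference-in-difference estimates one package's effect minus the other's, and the stated parallel-trends assumption does not isolate either

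*Protocol article*

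**What the plan says.** The Study design section of the protocol article places all eight districts in one of two actively treated groups and adds: "Each group will serve as the ‘control’ for the other". The stated purpose is: "This design will help us evaluate independent and combined effect of MNCH interventions to address MNCH outcomes". No untreated district is described.

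The Statistical analysis section gives the estimator, "difference-in-difference estimates will be used to assess the impact of the intervention on outcomes", and the model term: "An interaction term between group (intervention/control) and survey wave (baseline/end-line) will be included in each model". The identifying assumption is worded as "assuming parallel trends within the two MNH and CH groups, in the absence of any intervention".

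On off-theme care, Study design says that the "population in control areas will continue to receive all the routine services which are part of the public sector standard of care", plus whatever their own group's package adds.

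On the workers who deliver the care:
- The Introduction gives LHWs awareness work on contraception, maternal and child health and nutrition, and also treatment of diarrhoea and acute respiratory infection.
- Activity 1.2 ties training content to the district's theme, and Activity 1.4 does the same for commodities.
- The list of strengths and limitations includes: "Challenges of working with or assessing role of lady health workers who are already overburdened with competing priorities".
- Activity 2.1 has LHWs teach danger signs from pregnancy through childhood, with no limit by theme.

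**The concern.** Parallel untreated trends are enough when the control group stays untreated. Here the control group receives a different package, delivered partly by workers who also provide the care that the outcome measures. If the CH package changes maternal or newborn outcomes, or the MNH package changes child outcomes, that change enters the interaction with its sign reversed.

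Worsening of off-theme care in the control districts would then be scored as benefit of the other package. Improvement there would hide part of a real benefit. The interaction alone shows neither. This matters because, according to Study design, government and other partners have agreed to take up the interventions if the evidence suggests that they are effective and feasible at scale.

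**Working it through.** **1. What the interaction estimates.** For one outcome, let s be the common change that would occur without any intervention (the parallel-trends assumption), A the effect of the on-theme package, and B the effect of the other package on the same outcome.

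- Change in the on-theme group = s + A
- Change in the control group = s + B
- Interaction = (s + A) − (s + B) = A − B

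Parallel trends remove s. They do nothing about B. The interaction equals A only if B = 0, which is a separate assumption.

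**2. Inputs for the illustration.** The Sample size section gives a perinatal mortality baseline of 75 per 1000 with a 20% reduction, and a post-neonatal death baseline of 19 per 1000 with a 30% reduction. The planned effects are 0.20 × 75 = 15 per 1000 and 0.30 × 19 = 5.7 per 1000. The documents give no figure for B. The values below (5% or 10% worsening, 5% improvement) are assumptions, with the same baseline taken in both groups and s = 0. Post-neonatal death is the rate used to size the CH surveys; it is not a primary outcome in Table 2.

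**3. Off-theme worsening.**
- Post-neonatal death: 5% of 19 = 0.95 and 10% of 19 = 1.9 per 1000. As shares of 5.7 these are 17% and 33%. A true 30% reduction with 5% worsening in the MNH districts reads as 5.7 + 0.95 = 6.65 per 1000.
- Perinatal mortality: 5% of 75 = 3.75 and 10% of 75 = 7.5 per 1000, the latter half of the planned 15. A true 10% reduction with 10% worsening in the CH districts gives −7.5 − 7.5 = −15 per 1000, the absolute contrast expected from the full 20% effect. As a ratio it is 1 − 0.90/1.10 = 18.2%.

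**4. Off-theme improvement.** A true 20% perinatal reduction with 5% improvement in the CH districts gives −15 − (−3.75) = −11.25 per 1000, or 1 − 0.80/0.95 = 15.8% as a ratio. The bias now runs towards the null.

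**5. What within-group changes can and cannot show.** Compare two cases for perinatal mortality:

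| Case | s | A | B | On-theme change | Control change | Interaction |
|---|---|---|---|---|---|---|
| General decline in outcomes, effective package | +15 | −15 | 0 | 0 | +15 | −15 |
| No effect, off-theme worsening | 0 | 0 | +15 | 0 | +15 | −15 |

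The two cases look identical. Within-group changes show that the control group drives a contrast, but not why. They justify cautious wording; they do not justify a rule that rejects every contrast without improvement in the on-theme group.

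**The case against.** Displacement is not documented. The limitation about LHWs concerns working with them and assessing them; it does not say that project work crowds out routine care. The sentence on routine services answers an ethical concern about withheld interventions and is not an analytic assumption. LHWs are one channel among several: Table 1 puts their coverage at 50% to 80%, the Introduction says that about 70% of the population uses private providers, and attending births is not among the LHW tasks listed there. All of this stands, and it is why no size can be claimed.

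The plan also does not rest on the interaction alone. Study outcome measures defines the perinatal outcome as a reduction from baseline, Sample size uses a before-and-after comparison, and Statistical analysis plans frequencies at each wave. A benefit produced wholly by worsening in the control group would show no fall from baseline in the on-theme group. This stands in part: the information will exist, but the analysis section gives it no role in the impact estimate and no use as a check on off-theme care.

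Reporting detail may sit in an analysis plan that is not shown. That covers table layout. It does not cover the assumption, because the article itself states one, and that one is insufficient for a comparison of two treated groups.

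A reader might infer that the bias must exaggerate benefit. The documents do not support this: danger-sign messages span both themes, and the data-quality work in Activities 3.1 and 3.2 is not limited by theme, so dilution is also possible. A reader might also infer that the same individuals serve both groups. They do not; the groups are different districts, and the overlap of tasks is within each district.

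**Conclusion.** The point holds as one of identification. Under the stated assumption the interaction estimates the difference between two packages' effects on an outcome. It estimates one package's impact only if the other package leaves that outcome unchanged, and the analysis section does not say so. This follows from the design and needs no assumed figure.

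Direction and size are open. Each 1% of off-theme change moves the estimate by 0.75 per 1000 for perinatal mortality and 0.19 per 1000 for post-neonatal death, up or down. The figure of 17% to 33% of the planned post-neonatal effect rests on an assumed 5% to 10% worsening and is an illustration, not a forecast.

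The documents do not support the stronger conclusion that a positive result would be harm mistaken for efficacy. They make displacement plausible, make spillover plausible too, and already provide for change from baseline to be seen.

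**What to change.** In the Statistical analysis section:

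1. State the second assumption: each package has no effect on the other theme's outcomes. Say that without it the interaction is a difference between packages.
2. For every primary and coverage outcome, report both within-group changes from baseline with confidence intervals beside the interaction.
3. Pre-specify the off-theme survey outcomes in Table 2 as a check for harm or spillover: treatment and care-seeking for diarrhoea and pneumonia in MNH districts; antenatal care, skilled attendance and institutional delivery in CH districts.
4. Where change in the control group largely drives the contrast, describe it as a difference between packages and not as the impact of one.

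Do not make within-group improvement a strict condition for claiming impact; it would reject a real effect against a general decline. Treat trends in the LHW registers (Activity 3.2) as supportive only, because the project also works to improve recording, so those trends mix activity with reporting.

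The cost is some wording and a few table columns, using surveys already planned. The downside is that some positive interactions would be interpreted more cautiously.

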### Ethics and dissemination

Ethics approval of the study was obtained from the Aga Khan University
Ethics Review Committee on 28^th^ February 2017. In addition, ethical clearance was
sought from National Bioethics Committee (NBC), Pakistan.

Given the large scope of the UeN project, it is essential to garner support from and share the progress and findings of the study with the stakeholders. Therefore, stakeholder engagement activities will be conducted at different levels to inform policy, community and district health authorities.

**Participation in provincial child survival technical groups**

For reducing diarrhoea and pneumonia incidence, UNICEF has initiated the establishment of provincial child survival committees in which the UeN will participate. There are also existing provincial MNCH committees where AKU will have a seat by virtue of existing projects and the current UeN project. The UeN project will set up a system of monthly meetings with UNICEF and will share the project’s progress and activities.

**Formation of project advisory committee at national level**

Moreover, National Ministry of Health Services Regulation and Coordination will be requested to constitute a project advisory committee to help guide the UeN project through the existing federal ministry of health services and regulation to ensure coordination. The committee will meet once during the inception phase to discuss the project structure and remit, followed by bi-annual progress reviews to discuss challenges in implementation and address with appropriate actions.

**Patient and public involvement**

The public was not involved in the design of the research tools but they will be a part of the study and their feedback will be sought regarding intervention acceptability. The key findings will be shared with their representatives as part of the dissemination plan at local level.
